# Does menopausal hormone therapy (MHT), exercise or a combination of both, improve pain and function in post-menopausal women with greater trochanteric pain syndrome (GTPS)? A randomised controlled trial

**DOI:** 10.1186/s12905-016-0311-9

**Published:** 2016-06-16

**Keywords:** Hormone therapy, Exercise, Gluteal, Oestrodiol, Post-menopausal, Greater trochanteric pain syndrome, Tendinopathy

## Abstract

**Background:**

Greater trochanteric pain syndrome (GTPS) is pathology in the gluteus medius and minimus tendons and trochanteric bursa that causes debilitating tendon pain and dysfunction, particularly in post-menopausal women. Limited evidence in clinical studies suggests hormone changes after menopause may have a negative effect on tendon. This protocol describes a randomised controlled trial comparing the effectiveness of menopausal hormone therapy (MHT) and exercise therapy in reducing pain and dysfunction associated with GTPS in post-menopausal women.

**Method:**

One hundred and sixteen post-menopausal women will be recruited and randomised to receive one of two exercise programs (sham or targeted intervention exercise) and transdermal creams (MHT cream containing oestradiol 50mcg and norethisterone acetate 140mcg or placebo cream). Interventions will be 12-weeks in duration and outcomes will be examined at baseline, 12-weeks and 52-weeks. The primary outcome measure will be the VISA-G questionnaire and secondary outcomes measures will include three hip pain and function questionnaires (Hip dysfunction and Osteoarthritis Outcome Score, Oxford Hip Score, Lateral Hip Pain questionnaire), a global change in symptom questionnaire (using a 15-point Likert scale) and a quality of life measure (AQoL-8D questionnaire). Data will be analysed using the intention to treat principle.

**Discussion:**

This study is the first randomised controlled trial to compare the effectiveness of menopausal hormone therapy therapy alone, and with the combination of exercise therapy, to treat pain and dysfunction associated with GTPS. This study has been pragmatically designed to ensure that the interventions in this study can be integrated into policy and clinical practice if found to be effective in the treatment of GTPS in post-menopausal women. If successful, there is potential for this treatment regimen to be explored in future studies of other persistent tendon conditions in the post-menopausal population.

**Trial registration:**

Australian New Zealand Clinical Trials Registry ACTRN12614001157662 Registered 31 October 2014.

**Electronic supplementary material:**

The online version of this article (doi:10.1186/s12905-016-0311-9) contains supplementary material, which is available to authorized users.

## Background

Greater trochanteric pain syndrome (GTPS) is an overarching term used to describe a degenerative condition of the gluteus medius and minimus tendons (gluteal tendinopathy) and trochanteric bursa (trochanteric bursitis). The condition is characterised by intermittent or continuous pain at, or around, the greater trochanter of the femur [1], often with long-term pain and disability. Greater trochanteric pain syndrome most commonly affects post-menopausal women between 45 and 63 years old [2] and is severely debilitating, resulting in limited activity, quality of life, employment and capacity to exercise. The reported incidence of GTPS is 1.8 per 1000 patients per year in primary care [2] and prevalence rates of 23.5 % in women at risk of knee osteoarthritis [3] and 54 % in recipients of renal transplants [4]. These statistics likely underestimate the prevalence of GTPS since misdiagnosis and lack of recognition of GTPS are common.

The increased prevalence of GTPS in post-menopausal women [2] suggests that deficits in female sex hormone may be implicated in the condition. A number of risk factors for tendinopathy are associated with levels of circulating female sex hormones - advancing age, female gender and body composition [5, 6]. In pre-menopausal women, the likelihood of developing lower limb tendinopathy is lower than that of age matched men [7]. In post-menopausal women, as oestrogen levels decline, collagen production declines, tendon becomes thinner [8] and rates of tendon pathology and the likelihood of tendon rupture increases [9]. It is known that supplemental oestrogen is beneficial for increasing skeletal muscle strength [10], reducing fractures [11], preserving bone mass [12] and preventing a decline in the collagen content of skin [13]. It is feasible that supplemental oestrogen in the post-menopausal population may also preserve tendon collagen [8] and decrease tendon abnormality [6].

Despite this theory, current knowledge of the physiological effect of female sex hormone on tendon is limited [14–16], with some evidence of increased type 1 collagen upregulation and turnover [17–19], increased fibroblast proliferation [20, 21] and inhibition of pro-inflammatory cytokines [18, 22]. Animal studies also point to the upregulation of relaxin receptors and a resultant effect on the extracellular matrix of the tendon [23], however the literature is limited, inconsistent and generally of poor quality. A small number of observational studies [6, 17, 19, 22, 24–26] and one poorly designed randomised controlled crossover study [18] have investigated the effects of hormone therapy on the Achilles and patellar tendon. None of these studies examined patient reported outcome measures (pain, function, quality of life) to evaluate the effects of such interventions. As yet, there are no studies looking at the effects of menopausal hormone therapy (MHT) on gluteal tendon and no rigorous prospective RCT’s have been published in any other tendon. In addition, the optimal dosage, duration and method of administration of MHT to affect molecular, mechanical, and morphological tendon outcomes are unknown.

Traditionally, physiotherapy and exercise are first line interventions in the clinical management of tendinopathy [27–32] with any form of injection (e.g. cortisone, platelet rich plasma or autologous blood) and operative interventions offered subsequent to conservative tendon management [33, 34]. However, for gluteal tendon conditions, an abundance of research exists for both injection and operative methods and little exists for conservative treatment options [35]. If like other lower limb tendons, the gluteal tendons are responsive to load, then a similar treatment algorithm used in that of the patellar and Achilles tendon [36], should be effective in reducing pain and dysfunction.

The most recent systematic review on the effects of treatment of gluteal tendinopathy concluded that there was a need to conduct further randomised controlled trials [35]. Treatment interventions investigated included shockwave therapy, ‘home training’, corticosteroid injections and operative procedures (arthroscopic and open bursectomy, ilio-tibial band release, open bursectomy, tendon reattachment, trochanteric reduction osteotomy and endoscopic repair of gluteus medius tears). Only 1 out of the 14 included studies used exercise as an intervention [37]. Rompe et al. [37] compared a home training program involving progressive slow repetitive exercise (piriformis and ilio-tibial band stretching, straight leg raise, wall squat with ball and gluteal strengthening) with shock wave therapy and corticosteroid injection [37]. Exercise therapy was found to be less superior to corticosteroid injection at 1 month follow up but more superior at the 15 month follow up, indicating the longer-term benefits of exercise therapy. This response is similar to that seen in other tendons [38–40]. This review demonstrates that the role of exercise therapy in the management of greater trochanteric pain syndrome needs further investigation.

The proposed study will investigate two feasible management options for post-menopausal women with GTPS - hormone supplementation and exercise. The aim of this study is to investigate the effect of menopausal hormone therapy and exercise on pain and function in post-menopausal women with GTPS. We hypothesise that supplemental hormones and exercise may be beneficial for reducing pain and dysfunction measured by a clinical significant change in VISA-G scores and a significant improvement in quality of life measures. If successful, there is potential for this treatment regimen to be explored in future studies of other persistent tendon conditions such as Achilles, rotator cuff and lateral elbow tendinopathy in the post-menopausal population.

## Methods

The trial has been registered on the Australian New Zealand Clinical Trials Registry (ACTRN12614001157662) and has a Universal Trial Number (U1111-1160-2743). Protocol modifications will be approved by the ethics committee and communicated via the ANZCTR.

### Ethical approval and consent

The trial has received ethical approval from the La Trobe University Human Ethics Committee (number 14-055). Prior to enrolment, all participants will provide written informed consent to participate in the study, and for the publication of this manuscript (Additional file 1). Ethical standards will adhere to the National Health and Medical Research Council (NHMRC) National Statement [43] and the World Medical Association’s Declaration of Helsinki [44].

### Design

This study is a randomised 2 x 2 factorial trial with a 12-week intervention period and outcomes measured at baseline, 12-weeks and 52-weeks (Fig. 1). Reporting of this study will be formatted according to the Consolidated Standards of Reporting Trials (CONSORT) 2010 statement [45, 46] and incorporates the Standard Protocol Items: Recommendation for Interventional Trials (SPIRIT) [41].

**Fig. 1 Fig1:**
[figure not shown]
Gluteal La Trobe Trial (GLoBE) Profile

### Participants

#### Recruitment

Post-menopausal women with GTPS will be recruited through medical practitioners and healthcare professionals. Further advertising on community noticeboards, social media, Melbourne radio, newspapers and the Gumtree advertising service will also be conducted. Interested volunteers will contact the chief investigator (CG) via phone or email and will be screened for eligibility (Table 1).

**Table 1 Tab1:** Eligibility criteria

Inclusion Criteria	Exclusion Criteria
• Post-menopausal women, >52 weeks of amenorrhea and a serum oestradiol of 0-120pmol/L and an FSH of >20 IU/L • Lateral hip pain reproduction in 3 of 5 pain provocation tests (Trendelenburg test, palpation of the greater trochanter, FABER, resisted external derotation test, modified resisted external derotation test) • Have sufficient English skills to be able to read and understand the information and consent form due to the risks involved with participating in the study.	• Known adverse reaction to any form of hormone therapy • Use of any form of female hormone supplementation within the last 12 weeks • Display high risk factors for deep vein thrombosis (DVT) using the Wells score system [85] and/or pulmonary embolism (PE). • Current smoker • History of stroke, severe menstrual migraine, endometrial sarcoma, breast cancer, severe hyperlipidaemia, chronic liver disease, thyroid disease, lupus, hysterectomy and oophorectomy • HbA1c >8 % • Current cholecystitis, fibroids or undiagnosed abnormal uterine bleeding • Platelet-rich plasma (PRP), analogous blood injection (ABI) or corticosteroid injection into the hip region in the last 12 weeks • History of hip trauma or surgery on the affected side • Any other musculoskeletal, neurological and cardiorespiratory condition/s affecting their ability to participate in the study.

### Study procedure

#### Telephone screening

Potential participants will initially be screened via telephone to exclude those with obvious medical risk factors to MHT (Table 1). Further exclusion is warranted if the potential participant has received hormone therapy supplementation or invasive procedures (including injection) around the hip in the previous 12 weeks. If no obvious exclusion criteria exist, the participant will be referred for medical assessment.

#### Medical assessment

Participants found to be eligible after the phone screening will be invited to attend a medical examination by a sports physician. Upon presentation to their medical examination, participants will again be educated on the nature of the trial and asked to provide informed consent. Potential participants will be advised at that point that inclusion in the trial is on the provision that their medical history, clinical examination, blood samples and electrocardiograph (ECG) meet inclusion criteria.

The medical consultation will involve a full medical history to determine risk factors that would contraindicate the use hormone supplementation, and perform a clinical examination for the presence of greater trochanteric pain. Medical history will detail the history of presenting condition, family history, past medical history, social history (demographics, occupation, and recreation/activity participation), medication usage, substance use/abuse (alcohol, recreational drugs, smoker status) and allergies.

Clinical assessment to assess GTPS will involve five clinical pain provocation tests. Tests will include the Trendelenburg test [41], palpation of the greater trochanter [42], the Patrick-Faber test [43], resisted external de-rotation test [41] and modified external de-rotation test (increased hip adduction moment). Participants are asked if testing reproduces reported symptoms or pain, the location of the symptoms and intensity of pain on a 0–10 Visual Analogue Scale (VAS). A positive test is defined as a spontaneous reproduction of the participant’s lateral hip pain. To be eligible for the trial, clinical testing must reproduce pain in 3 of 5 pain provocation tests.

Where a participant meets inclusion criteria and has not had a platelet-rich plasma (PRP), analogous blood injection (ABI) or corticosteroid injection in the hip region in the last 3 months, but is excluded from the hormone intervention on medical grounds, they will be randomised into a single arm (intervention exercise or sham exercise).

#### Blood sampling and electrocardiography

Participants who remain eligible for the study following medical consult, will be referred for blood tests and an electrocardiograph to confirm eligibility in the trial. Blood tests will examine lipid levels (fasting cholesterol, triglycerides, high density lipoprotein: HDL, low density lipoprotein: LDL), liver function (LFT), diabetes indicators (glucose, HbA1c), iron (Fe) studies and thyroid function (TFT). Serum levels of follicle stimulating hormone (FSH) and oestradiol will also be recorded as a baseline measure and compared to levels post pharmacological intervention. A 12 lead echocardiograph (ECG) will be undertaken to monitor if any arrhythmia or irregularities are present. Indicators for inclusion or exclusion of a participant will be made on clinical judgement by the treating physician, taking into account all individual tests results and their normative values.

Once deemed eligible for the trial, participants will be randomly allocated into an exercise group and a transdermal cream group. A participant may be randomised into one of the following 12-week interventions: (i) exercise therapy, placebo cream; (ii) sham exercise, MHT cream; (iii) sham exercise, placebo cream or (iv) exercise therapy, MHT cream.

### Sample size and power analysis

The sample size required for this RCT is 100 participants (25 in each group) to detect a minimal clinically important difference of 10 points on the VISA-G outcome measure, assuming a standard deviation of 13 (Alpha of 0.05 and a power of 80 %) [44]. To account for potential drop-out, we will recruit 116 participants (29 per group).

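### The stated inputs (10 points, SD 13, alpha 0.05, 80% power) do not give 25 per group for an unadjusted two-group comparison: they need 28, and 25 gives 76% power (minor)

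*Protocol article*

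**What the plan says.** The whole calculation is in the Protocol article, Methods, under Sample size and power analysis. It reads "The sample size required for this RCT is 100 participants (25 in each group) to detect a minimal clinically important difference of 10 points", and continues "assuming a standard deviation of 13 (Alpha of 0.05 and a power of 80" per cent. To allow for drop-out, "we will recruit 116 participants (29 per group").

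The section names no test, no sidedness, no contrast (one cell against another, or a factorial margin) and no correlation between baseline and follow-up scores.

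Two other sections bear on how to read the figure. Design says "This study is a randomised 2 x 2 factorial trial with a 12-week intervention period". Statistical analysis plans a mixed model ANCOVA that adjusts each outcome for its baseline value and estimates the difference between groups. It does not name a main effect, an interaction or a pairwise contrast as primary.

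**The concern.** The section gives a difference, an SD, an alpha and a power, and says that 25 per group follow from them. Apart from sidedness, these are all the inputs that a two-group sample size formula needs, so a reader can check the sum. The result does not come out at 25, one-sided or two-sided.

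What is at stake is how the result will be read. For the same 100 women and the same 10 points, power depends strongly on which contrast is meant: about 76% for one arm against another without adjustment, and about 97% for a factorial main effect. Someone interpreting a null result needs to know which figure applies, and the single 80% matches neither.

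**Working it through.** **Inputs.** All are from Sample size and power analysis, except the design.

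- Difference: 10 points on the VISA-G.
- SD: 13, so the standardised difference is 10/13 = 0.769.
- Alpha: 0.05. Sidedness is not stated; two-sided is assumed by convention and one-sided is also tried.
- Power: 80%.
- Stated result: 25 in each of four groups, 100 in total; 116 recruited (29 per group). The implied drop-out is 1 − 100/116 = 13.8%.
- Design: 2 × 2 factorial with equal groups, so each main effect compares 50 with 50.

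**Step 1. Try to reproduce 25 per group (two groups, two-sided, unadjusted).**

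Normal approximation: n = 2 × SD² × (z for 0.975 + z for 0.80)² / difference² = 2 × 169 × (1.960 + 0.842)² / 100 = 26.5, so 27 per group (108 in total).

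Noncentral t: n = 27.5, so 28 per group (112 in total).

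Neither gives 25.

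**Step 2. Power at 25 per group.**

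The standard error of the difference is 13 × √(2/25) = 3.68, and 10/3.68 = 2.72.

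- Normal approximation: Φ(2.72 − 1.96) = 77.6%.
- t test with 48 degrees of freedom: 76.0%.
- t test with the error term pooled over four groups (96 degrees of freedom): 76.8%.

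By t test, the difference detectable with 80% power is 10.5 points.

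**Step 3. Other readings of the same paragraph.**

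| Reading | Power for 10 points, 25 per group |
|---|---|
| Two groups, one-sided t test | 85.0% (80% would need 22 per group) |
| Factorial main effect, 50 v 50; SE = 13 × √(2/50) = 2.6 | 96.8% |
| Interaction of 10 points; SE = 13 × √(4/25) = 5.2 | 47.8% |
| Four-group F test, one arm 10 points from three equal arms | 79.0% (80% needs about 102 in total) |
| Four-group F test, means 0, 5, 5, 10 | 59.6% |

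The F test with a single differing arm comes closest, but the article does not state that basis. The interaction row only shows that this contrast does not explain the figure either; the section does not target an interaction of that size. For a main effect, the difference detectable with 80% power is 7.4 points by t test.

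**Step 4. The planned baseline adjustment.**

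If 13 is the unadjusted SD and r is the correlation between baseline and follow-up, the ANCOVA works with SD = 13 × √(1 − r²). The article gives no r, so these values are assumptions. The comparison is two groups of 25, two-sided.

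| Assumed r | Residual SD | Power, t (47 df) | Power, normal |
|---|---|---|---|
| 0 (no adjustment; 48 df) | 13.0 | 76.0% | 77.6% |
| 0.25 | 12.6 | 78.6% | 80.2% |
| 0.30 | 12.4 | 79.7% | 81.4% |
| 0.50 | 11.3 | 86.8% | 88.1% |

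By t test, 80% is reached at r of about 0.31; with the four-group error term, at about 0.28.

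**Step 5. The recruited number.**

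If all 29 per group were retained, the unadjusted two-group t test would have 82.1% power; with 28 retained, 80.7%; with 27, 79.2%.

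**The case against.** The strongest reply is that an unadjusted t test is not the planned analysis. The article plans a baseline-adjusted ANCOVA, and a modest correlation of about 0.3 brings 25 per group up to 80%. This stands as far as it goes: nobody can say from the article that the planned analysis falls short of 80%. It does not rescue the paragraph, which mentions neither adjustment nor a correlation and presents 25 as what the listed inputs require.

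A second reply is that a condensed article may leave the test, contrast and sidedness to a fuller document. That also stands, and their absence is not the complaint here. The complaint is that the printed number does not follow from the printed inputs.

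Third, the gap is small, and the 29 recruited per group exceed the 28 needed. That supports a low grade. The extra women are there to cover drop-out, however, so on the unadjusted reading the margin suffices only if no more than one in 29 per group is lost.

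Three stronger readings are tempting, and the article supports none of them:

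- A reader might infer that the trial is underpowered. Main effects have about 97% power for 10 points, and the ANCOVA may well reach 80% for a pair of arms.
- A reader might infer that the 80% fits nothing the trial will report. The ANCOVA is what it will report, and with a plausible but unstated correlation the figure could be right for it.
- A reader might infer much lower power after correction for many pairwise tests. The article specifies no such set of tests and no such correction.

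**Conclusion.** The point holds as a minor error in the statement. With a 10-point difference, SD 13 and alpha 0.05 taken as two-sided, an unadjusted comparison of two groups needs 28 per group by t test (27 by the normal approximation), not 25. At 25 per group the power is 76% (78%) rather than 80%. That is 2 to 3 women per group, about 4 percentage points, or half a point on the VISA-G.

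The conclusion rests on reading the paragraph as an unadjusted two-group comparison. Sidedness does not decide it, since a one-sided test does not return 25 either. The conclusion concerns the stated figure and is not a judgement that the trial is too small.

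**What to change.** Restate the paragraph so that each figure belongs to a named contrast, for example:

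> With 25 evaluable women per group, an unadjusted two-sided comparison of two groups has 76% power for a 10-point VISA-G difference (SD 13, alpha 0.05). Each factorial main effect (50 v 50) has 97% power for 10 points and 80% power for 7.4 points.

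This wording describes both contrasts without choosing the primary one, which the Statistical analysis section leaves open and the investigators should settle. If 80% at 25 per group is kept because of the ANCOVA, say so and give the baseline correlation used and its source.

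The cost is one paragraph. Recruitment, procedures and the planned analysis stay as they are. The only loss is that the printed power for a pair of arms becomes slightly less favourable.

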### Randomisation, allocation and blinding

A block randomisation schedule will be generated using a web based randomisation program (https://www.randomizer.org/) with the sequence tranferred onto a computer spreadsheet by a researcher external to the trial investigators, who will have no contact with participants throughout the duration of the trial. This external researcher will complete concealed allocation of participants to groups in accordance with the randomisation schedule. All data collected will be de-identified and only made accessible to the study investigators.

Participants will be blinded to allocation for both the exercise therapy and hormone therapy group. Placebo creams and sham exercise groups, may increase the success of participant blinding [46]. The success of blinding will be formally measured during week 1 of the trial by asking participants to indicate which group for both interventions they believe they are allocated to. It is important to assess the success of blinding to determine if protection against participant expectation effects is maintained [46]. The treating physiotherapists will be blind to cream type, but due to the nature of the intervention, cannot be blinded to exercise group. Detailed training of physiotherapists will be provided to ensure equivalent provision of care and motivation for both groups [47]. Unblinding of a participant and trial investigators to cream allocation will only be permissable in the unlikely event of an adverse reaction requiring medical team involvement.

Data analysts and outcome measure assessors will be blinded to group allocation. This will be achieved through direct communication from the external researcher preparing the randomisation schedule to the trial physiotherapist implementing the exercise intervention and the pharmacist implementing the hormone cream intervention.

